## Abstract

**Introduction:**

Data suggest that micronised progesterone (mP) in menopausal hormone therapy is safer for the breast than synthetic progestins, while protection of the endometrium appears to be less effective. However, comparative randomised trial data are lacking. The objective of the Progesterone Breast Endometrial Safety Study is to investigate breast and endometrial safety of mP versus norethisterone acetate (NETA) in continuous combination with oral oestrogen.

**Methods and analysis:**

This multicentre trial, conducted at three University Hospitals in Stockholm and Uppsala, Sweden, consists of two phases: part 1 focuses on breast safety and is designed as a double-blind, randomised controlled trial. 260 postmenopausal women will be randomised to 100 mg mP or 0.5 mg NETA per day in continuous combination with 1 mg oestradiol. The primary objective is to compare the treatments with respect to percentage change in mammographic breast density after 12-month treatment. Secondary outcomes are breast proliferation, endometrial histology and proliferation, bleeding pattern, gut and vaginal microbiome, hormone levels and coagulation and metabolic factors, mood, and health-related quality of life. Part 2 features an open, single-arm design to study endometrial safety of 1-year treatment with mP in continuous combination with oestradiol on endometrial pathology (hyperplasia and cancer). We will treat 260 additional women with 100 mg mP/1 mg oestradiol resulting in an endometrial safety population of 390 women. The total number of participants in part 1 and part 2 will be 520.

**Ethics and dissemination:**

The study protocol was approved by the Swedish Ethical Review Authority (2021-03033) on 29 June 2021 with amendment (2023-01480-02, protocol version 3.1) on 14 March 2023. Results of the study will be published in peer-reviewed journals and presented at scientific meetings.

**Trial registration number:**

NCT05586724.

STRENGTHS AND LIMITATIONS OF THIS STUDYThis is a double-blind, multicentre randomised controlled trial investigating both breast and endometrial safety of micronised progesterone versus norethisterone acetate in continuous combination with oral oestrogen.Study treatment is limited to 1 year.Mammographic breast density will be evaluated as a surrogate marker for breast cancer and endometrial pathology as a surrogate marker for endometrial cancer.All mammograms and endometrial biopsies will be evaluated by assessors blinded to the patient’s identity and type of treatment.Another strength is that data will be collected by a digital platform.

## Introduction

 Menopausal hormone therapy (MHT) for climacteric symptoms in women started in the 1960s and reached its peak in the late 1990s. Most scientific reports from observational studies published at that time showed the beneficial effects of MHT on women’s health.^1^,^3^ However, these promising findings were thereafter overturned when the first results of the Women’s Health Initiative (WHI) randomised controlled trial were published in 2002.^4^ The trial was terminated early due to increasing rates of cardiovascular disease, breast cancer and stroke among postmenopausal women using conjugated equine oestrogen plus medroxyprogesterone acetate therapy.^5^,^7^ Despite the concerns raised for the generalisability of the WHI findings, mostly focused on older age of women (mean age 63 years) and long periods after menopause (>10 years),^8^ the number of women treated with MHT subsequently greatly diminished because of fear of risks with the treatment.^9 10^

There is a great need to find safe MHT able to control excessive endometrial stimulation from the oestrogen component without stimulatory effects on the breast by the combination of oestrogen/progestogens. Combinations of oestradiol and synthetic progestins, particularly norethisterone acetate (NETA), remain the most common types of MHT used in the Nordic countries. Long-term treatment with oestrogens in combination with synthetic progestins is associated with a small but known increased risk of breast cancer,^11^,^13^ whereas the risk of endometrial cancer with continuous combined MHT is decreased.^4 14 15^

Micronised progesterone (mP) was first introduced in the late 70s. At present, it is gaining in popularity in combination with oral or transdermal oestradiol as MHT in many European countries. Observational studies indicate a lower risk of breast cancer using mP in combination with oestrogen compared with combinations with synthetic progestins.^13 16 17^ On the other hand, observational studies indicate a higher risk of endometrial cancer with mP compared with progestins,^18^,^20^ whereas randomised trials have shown adequate endometrial safety with mP combined with oestrogen.^21^,^23^ Recent international guidelines recognise combinations with mP as potentially safer than progestogens for the breast but data from randomised trials are requested.^24 25^ There is a need to obtain increased knowledge from randomised controlled trials about the balance between breast and endometrial safety of mP versus progestins in combination with oestrogen.

The aim of this double-blind, multicentre, randomised, controlled trial is to compare the effects of 12-month treatment with mP versus NETA, both in combination with oestradiol, on breast and endometrial safety in healthy postmenopausal women. The primary outcome is mammographic breast density as this is the strongest independent risk factor for breast cancer.^26^ Endometrial safety will be evaluated as a composite measure of endometrial hyperplasia and cancer.

## Methods and analysis

### Objectives and study design

This study is a double-blind, multicentre randomised controlled trial investigating both breast and endometrial safety of mP versus NETA in continuous combination with oral oestrogen (Eudract: 2021-001624-17 and ClinicalTrials.gov: NCT05586724). The trial is divided into two parts described below: part 1 is a double-blind, multicentre, randomised, controlled trial comparing the two treatments with respect to breast safety as primary objective (figure 1), and part 2 is an open, single arm to study endometrial safety of mP in continuous combination with oestradiol (figure 2).

**Figure 1 F1:**
[figure not shown]
Flow diagram of part 1: breast safety—a double-blind, randomised study design. mP, micronised progesterone; NETA, norethisterone acetate.

**Figure 2 F2:**
[figure not shown]
Flow diagram of part 2: endometrial safety—an open single-armed study design. mP, micronised progesterone.

#### Part 1: breast safety: a double-blind, randomised study design

##### Primary objective

To evaluate the effects of 12-month treatment with mP versus NETA, both in combination with oestradiol, on mammographic breast density.

##### Secondary objectives

To compare the effects of 1-year treatment with mP versus NETA, both in combination with oestradiol on the following parameters:

Breast cell proliferation.Endometrial histology and proliferation.Endometrial thickness using ultrasound.Bleeding pattern.Gene and protein expression of growth factors and apoptosis markers in breast and endometrial tissue.Vaginal and gut microbiome.Blood levels of serum hormones, growth and metabolic factors, lipid profile, coagulations factors.Scores on validated questionnaires: depression and anxiety symptoms, health-related quality of life, Women’s health (menopausal symptoms).

### Part 2: endometrial safety: open, single-arm, study design

#### Primary objective

To evaluate the effect of 12-month treatment with mP in continuous combination with oestradiol on endometrial pathology (hyperplasia and cancer).

### Study population and recruitment

Healthy postmenopausal women aged 45–60 years with climacteric symptoms will be recruited from existing cohorts, women’s clinics and by advertisement in local newspapers and social media. Interested women are asked to respond by email and are subsequently contacted by telephone by a research midwife for an initial screening. Those judged to be preliminary eligible at telephone screening are sent written information about the study and invited to a screening visit for informed consent and assessment of inclusion and exclusion criteria as specified below.

When all 260 women in part 1 have been included, recruitment for part 2 will start.

### Inclusion criteria

Healthy and naturally postmenopausal women (more than 1 year since last menstruation or follicle-stimulating hormone (FSH)>40 IE/L) with climacteric symptoms (sweating, hot flush and/or sleep problems) that adversely affect the quality of life.Age 45–60 years.Body mass index >19 kg/m^2^ and ≤32 kg/m^2^.Intact uterus.In case of previous MHT use, washout 8 weeks for oral MHT and 4 weeks for transdermal MHT or local oestrogen treatment before screening.Written informed consent.

### Exclusion criteria

A history or risk factors for breast cancer, breast cancer in situ or abnormal mammogram at baseline as assessed clinically by a radiology expert.A history or risk factors for endometrial cancer or hyperplasia or abnormal/proliferative endometrial biopsy at baseline.Vaginal bleeding.Any concomitant medical treatment except for well-controlled hypertension, non-insulin-treated type 2 diabetes, asthma and hypothyroidism.History or the presence of or risk factor for cardiovascular disease including thromboembolic disorder or cerebrovascular disease.History or the presence of liver and gallbladder disease, familial hyperlipidaemia, epilepsy or classical migraine with aura.A history or the presence of clinically significant depression or other psychiatric disorder that might in any way compromise the performance of the trial or undermine its scientific validity.Porphyria, systemic lupus erythematosus and otosclerosis.Current use of MHT or local oestrogen treatment.Alcohol and/or drug abuse.Clinically significant findings on physical and/or gynaecological examination at baseline.Hypersensitivity to any of the study treatments.

### Interventions

#### Part 1: breast safety: a double-blind, randomised study design

Two parallel groups of postmenopausal women will be randomised to 12-month treatment of:

Group A: Capsule 100 mg mP (Utrogestan) orally per day in continuous combination with 1 mg encapsulated oestradiol (Estrofem).

Group B: Capsule 0.5 mg NETA/1 mg oestradiol (Activelle) orally per day (encapsulated and identical to Estrofem) and one matched placebo capsule to Utrogestan.

### Part 2: endometrial safety: open, single-arm, study design

In this open part of the study, all women will take a capsule of 100 mg mP (Utrogestan) orally per day in continuous combination with tablet 1 mg oestradiol (Estrofem) for 12 months.

### Randomisation

In part 1, patients will be randomised (in a 1:1 ratio) to 12 months of study treatment. The randomisation list will be created electronically using random permuted blocks with a random block size of a maximum of 6. This will be carried out by Apotek Produktion & Laboratorier and kept at the Karolinska University Hospital pharmacy. All personnel involved directly in the study shall be unaware of the treatment assigned until study closure and completion of analyses. Mammography examinations will be performed at different centres; however, evaluation of mammograms will be performed centrally by independent specialists blinded to treatment. Collection of breast biopsies will be performed only at Karolinska University Hospital. As no effect of centres is assumed, randomisation will be pooled over the centres.

### Study assessments and procedures

The study will be performed at three university hospitals in Sweden: Karolinska University Hospital, Stockholm, Danderyd Hospital, Stockholm and Uppsala University Hospital, Uppsala. The study assessment and procedures are presented in table 1.

**Table 1 T1:** Study visit procedures

Test or procedures	Screening visit	Baseline visit	1-month contact	3-month visit	6-month visit	9-month visit	End of study visit	13-month contact
Informed consent	x							
Medical history	x							
Inclusion criteria	x	x						
Exclusion criteria	x	x						
Blood sample	x*	x†					x†	
Physical examination‡	x	x					x	
Gynaecological examination§	x	x					x	
Endometrial biopsy		x					x	
Mammography¶		x					x¶	
Breast biopsy**		x					x**	
Microbiota sample		x					x	
Questionnaire††		x		x	x	x	x	
Randomisation		x						
Compliance			x	x	x	x	x	
Vital signs‡‡				x	x	x	x	
Adverse events			x	x	x	x	x	x

* Safety parameters including hematologyhaematology, lipids, liver enzymes.

† Fasting blood sample for analysis of hormones, metabolic factors, and coagulation factors.

‡ Body weight, blood pressure, breast examination, cor, pulm.

§ Including vaginal ultrasound.

¶ A second mammography only in Ppart 1.

** Breast biopsies only in P part 1.

†† Depression and anxiety symptoms (PHQ-9, HADS), Hhealth-related quality of life (PGWB), Women’s Health Questionnaire ().

‡‡ Including bodyweight, blood pressure.

HADSHospital Anxiety and Depression ScalePGWBPsychological General Well-Being IndexPHQ-9Patient Health Questionnaire-9

#### Screening visit

At the screening visit, the woman will be informed orally and in writing about the study and will have the opportunity to ask questions. If she agrees to participate, she will sign an informed consent form (online supplemental material). The patient will be given a copy of the fully signed consent signed by herself and the investigator/coinvestigator. Thereafter, she will undergo a physical examination, gynaecological assessment and blood sample for measurement of safety parameters including haematology, lipids and liver enzymes.

#### Baseline visit

At the baseline visit, the investigator will review inclusion/exclusion criteria again to determine eligibility to participate in the study. The visit is in the morning for collection of a fasting blood sample for analysis of hormones, metabolic factors and coagulation factors. Furthermore, there will be measurements of body weight and blood pressure, gynaecological examination including vaginal ultrasound, endometrial biopsy and microbiome samples from vagina and rectum, mammography, and breast biopsy (Stockholm-centres only) (part 1), and self-assessment of depression, anxiety, quality of life and menopausal symptoms. Eligible women will be randomised (part 1) to study treatment and start their study medication next day and asked to register any bleeding in their bleeding diary.

#### One-month telephone contact

One month after start of treatment, a research midwife will have a telephone contact with the patient for follow-up of symptoms, compliance and possible adverse events.

#### Three, 6 and 9 months visit

Physical visits will be performed at 3, 6 and 9 months for assessment of vital signs, body weight and blood pressure, compliance, drug tablet return and adverse events. Furthermore, the participants will fill in the same questionnaires as at baseline.

#### End of treatment (12 months)

At end of treatment, the same investigations as at baseline will be performed with the exception of a second mammography, which will only be performed in part 1.

#### Thirteen-month telephone contact

The study ends with a telephone contact with a research midwife.

### Discontinuing study treatment

Subjects may be discontinued from study for any of the following reasons:

Development of exclusion criteria during the course of the study.Serious adverse event.Significant protocol violation.Unacceptable toxicity.Failure to comply with study evaluations/visits which would prevent evaluation of drug compliance and supply.Other conditions for which, in the investigator’s opinion, it is in the subject’s best interest to be withdrawn from the study.

When a subject withdraws from the study, the reason for the withdrawal shall be recorded. Any subject who prematurely terminates participation and has received at least one dose of study drug will undergo end-of-study procedures. If study participation is terminated due to an adverse event possibly related to the study drug or study examinations, the subject must be followed up according to the medical judgement of the investigator.

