### Sample size calculation

#### Mammographic breast density: primary outcome in part 1

Based on data from the WHI study, it was shown that an increase in mammographic density by 1% during combined MHT corresponded to a 3% increase in risk of breast cancer.^42^ We estimated that a difference of at least 30% in treatment response between the groups would be clinically relevant. A power analysis based on our previous results,^27^,^30^ and assuming a 35% difference in treatment response, revealed that a patient material of 91 women/group would be sufficient to detect a significant difference in mammographic breast density between the groups at the 5% level (two sided) with 80% power. Considering the estimated rate of discontinuation and incomplete data (~30%), the target sample for this part of the study would be 260 patients.

#### Endometrial pathology: primary outcome in part 2

The reported 1-year background incidence rate for endometrial hyperplasia/cancer in postmenopausal women treated with authorised oestrogen/progestogen combinations is approximately 0%–1%.^18 19^ With a sample size of 300 women in the treatment arm mP+E, two or less women with serious adverse endometrial outcomes would result in an annual incidence of 0.67% or less with an upper bound of the one-sided 95% CI of 2.08% or less. Considering the estimated rate of discontinuation and incomplete data (~30%), the target sample for this part should be 390 patients, 130 women randomised to mP from part 1 and another 260 women from part 2.

The total number of patients in part 1 (n=260) and part 2 (n=260) will be 520.

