#### Statistical analysis

Analyses of primary and secondary outcomes will be based on an intention-to-treat (ITT) population (all subjects who have received at least one dose of study drug with a baseline evaluation meeting the entry criteria), as well as per-protocol population (subjects who have completed the study without major protocol deviations). The safety analysis population will comprise all patients who received at least one dose of the study drug.

The primary outcome variable mammographic breast density (part 1), expressed as percentage, will be compared between and within groups using the mixed model procedure with subjects as a random factor, and treatment (mP+E and NETA+E), time (baseline and exit) and treatment×time as fixed factors. Differences between groups will be evaluated by the interaction treatment×time, and differences within groups by the factor time, by holding the other factor (treatment) fixed.

Incidence of endometrial pathology (hyperplasia or cancer) in the mP+E group as endometrial safety (part 2) and based on histopathology will be expressed as incidence rate and 95% CI, in line with the European Medicines Agency guidelines.^43^

The secondary outcome variables (breast cell proliferation, endometrial cell proliferation, endometrial thickness using ultrasound, gene and protein expression of growth factors and apoptosis markers in breast and endometrial tissue, vaginal and gut microbiome, blood levels of serum hormones, growth and metabolic factors, lipid profile, and coagulations factors) will be analysed using the mixed model procedure with the same factors as above. In case of positively skewed distributions of these variables, log transformation will be performed prior to the analysis.

The Mann-Whitney U test will be used to compare the groups with respect to the changes in the PHQ-9, HADS, PGWB and WHQ and the Wilcoxon matched pairs test for changes in these variables within the groups.

If missing data occur in the ITT analysis, the method last observation carried forward (LOCF) will be used. Assuming missing data occur at random, patients with missing data can be included in the mixed model analysis, otherwise, we use the LOCF procedure. Correlations will be assessed by Spearman’s rank correlation test. A p<0.05 will be considered significant.

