Endometrial hyperplasia is a strong risk factor for endometrial cancer.^45^ We will evaluate endometrial histology in both part 1 and part 2 of the trial, but the randomised part (n=260) is not powered for evaluation of endometrial hyperplasia and cancer, and therefore, this part will be comparing endometrial histology and proliferation between the two treatment groups as secondary objectives. The combination of 0.5 mg NETA/1 mg oestradiol (Activelle) is standard treatment with a well-known endometrial safety profile. In contrast, the combination of 100 mg mP/1 mg oestradiol has only been evaluated for endometrial safety in one previous study,^23^ and therefore, we found it important to study the incidence of endometrial hyperplasia and cancer of this treatment compared with the background incidence rate as a primary objective in part 2 of the trial.

A potential limitation of the study is the duration of treatment of 1 year. This could be regarded as short term, but previous studies have demonstrated that change in mammographic density by hormone treatment develops as soon as after a few weeks.^46^ Moreover, based on the estimated incidence rate of endometrial pathology (hyperplasia and cancer), 1 year should be sufficient for assessment of endometrial safety.^43^

The strengths of the study include the double-blind, multicentre, randomised design and the sufficient number of patients to assess the primary outcomes according to power calculations. Other strengths are blinded assessment of both mammographic density and endometrial pathology. Furthermore, secondary outcomes include a deeper investigation of the treatment effects on breast and endometrial tissue, as well as assessments of subjective symptoms and health-related quality of life by validated questionnaires. In addition, the treatment effect on the gut and vaginal microbiome will be studied. All data will be collected by a digital platform, which will facilitate the extraction and compilation of data.

The study is expected to provide increased knowledge about breast and endometrial safety with mP compared with progestin in continuous combination with oestrogen. The results can then be part of the basis for updated national and international guidelines for hormone treatment in menopause.

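### Biopsies taken at early withdrawal can enter the part 2 endometrial incidence without an exposure rule, which would tend to lower a 12-month rate and its upper bound

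*Protocol article*

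**What the plan says.** All places are in the protocol article.

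- **Part 2, Primary objective:** the target is the effect of 12 months of micronised progesterone with oestradiol on endometrial pathology. Under Outcomes, the biopsy is planned at baseline and after 12 months.
- **Discontinuing study treatment:** "Any subject who prematurely terminates participation and has received at least one dose of study drug will undergo end-of-study procedures". Table 1 lists endometrial biopsy among the end-of-study procedures. No minimum exposure is given.
- **Statistical analysis, populations:** primary and secondary outcomes are analysed in an ITT set, "all subjects who have received at least one dose of study drug with a baseline evaluation meeting the entry criteria", and also in a per-protocol set of women who completed the study without major deviations. Neither is named as primary for endometrial safety.
- **Statistical analysis, part 2:** the incidence "based on histopathology will be expressed as incidence rate and 95% CI". The sentence does not say whether the denominator is women or woman-years.
- **Sample size calculation, part 2:** two cases in 300 women are called an annual incidence of 0.67%, with a one-sided 95% upper bound of 2.08%. Then: "Considering the estimated rate of discontinuation and incomplete data (~30%), the target sample for this part should be 390 patients".
- **Discussion:** on the length of treatment, "1 year should be sufficient for assessment of endometrial safety".

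**The concern.** A woman who stops after a few weeks and has a negative exit biopsy tells us little about the endometrium after a year of treatment. Under the ITT definition she nevertheless belongs to the analysis set, and under the withdrawal rule she has a biopsy to contribute. The sample size section works from a different number: 300 women, set apart from those expected to discontinue or have incomplete data. The article therefore points to two denominators for the same primary result.

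This matters more here than in a comparative analysis. Part 2 has no control arm. Its conclusion rests on one proportion and its upper bound, read against a background of about 0% to 1%. If early negatives enter freely, more early withdrawal makes the interval tighter and the treatment look safer.

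This differs from the question of carrying observations forward for missing biopsies. These women have real biopsies, so dropping last observation carried forward would not remove the problem.

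**Working it through.** **Inputs from the protocol article.** Target 390 women; about 30% discontinuation or incomplete data; planning example of 2 cases in 300 with a one-sided 95% bound. The timing of withdrawal is not given, so exposure times below are assumptions.

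**Step 1: reproduce the plan's figure.** The exact (Clopper-Pearson) one-sided 95% upper bound for x cases in n women is the 0.95 quantile of Beta(x + 1, n − x).
- 2/300 = 0.67%, upper bound 2.08%. This matches. A Poisson bound would be 2.10%, so the planning example is a binomial proportion of women.

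**Step 2: the two candidate denominators.** Early leavers, taking the whole 30%: 0.30 × 390 = 117. Completers: 390 − 117 = 273. (The 300 in the plan arises as 390/1.3, not 390 × 0.7; that is a separate point.)

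| Cases | 273 completers | 390, all leavers negative |
|---|---|---|
| 2 | 0.73% (bound 2.29%) | 0.51% (bound 1.61%) |
| 3 | 1.10% (bound 2.82%) | 0.77% (bound 1.98%) |

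This is the extreme: every non-completer returns and gives an evaluable, negative biopsy.

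**Step 3: how fast it shrinks.** With 3 cases, the bound falls to the plan's 2.08% only from about 371 evaluable women, that is 371 − 273 = 98 of the 117 leavers. At 351 evaluable women it is 2.19%.

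**Step 4: expected dilution.** Assume a true 12-month risk of 1% and a constant hazard λ = −ln(0.99). If a fraction d stops after a mean of m years, the expected crude ITT incidence is (1 − d) × 1% + d × (1 − exp(−λm)).
- d = 30%, m = 3 months: 0.78%
- d = 30%, m = 6 months: 0.85%
- d = 10%, m = 6 months: 0.95%

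The relative understatement is about 5% to 22% over this range.

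**Step 5: woman-years instead of women.** With 2 cases and 117 leavers, the denominator is 273 + 117m and the Poisson bound is 6.296 divided by it.
- m = 3 months: 302.25 woman-years, 0.66% (bound 2.08%)
- m = 6 months: 331.5 woman-years, 0.60% (bound 1.90%)
- m = 9 months: 360.75 woman-years, 0.55% (bound 1.75%)

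**Step 6: can the direction reverse?** Suppose 2 cases among 273 completers and 2 among the 117 leavers.
- Completers only: 2/273 = 0.73% (bound 2.29%)
- ITT: 4/390 = 1.03% (bound 2.33%)
- All cases over 12-month biopsies plus early cases: 4/(273 + 2) = 4/275 = 1.45% (bound 3.30%)

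So ITT can exceed the completers-only rate. It cannot exceed a rate that keeps the same cases and leaves out the early negatives.

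**The case against.** The strongest reply is that nothing in the article says an early biopsy counts as a 12-month result. A reader might infer that it does, from the ITT definition and the withdrawal rule together, but this remains an inference. The part 2 sentence speaks of an incidence rate, which could mean woman-years and would then credit only actual exposure. The baseline and exit time points named in the statistical section belong to the mixed model for breast density, so they cannot support the inference. This stands. Against it, the only worked example divides cases by women, so counting women is the more natural reading.

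Second, a completer analysis is already planned. That also stands, and the 12-month rate is not available only from a diluted set. But the per-protocol set requires completion, so a woman who develops hyperplasia and withdraws would leave the numerator. It replaces dilution with a possible loss of cases.

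Third, a reader might infer that the ITT rate always understates the risk. The documents do not support that. It requires risk to accrue with exposure and stopping to be unrelated to pathology; Step 6 shows the comparison with completers reversing.

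Fourth, a reader might infer that three cases would wrongly pass at 2.08%. The article uses 2.08% to illustrate precision and states no pass mark. The example also needs about 98 of 117 leavers to supply an evaluable negative biopsy, while the 30% expressly includes incomplete data.

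Finally, visit windows and the handling of early biopsies are often left to the analysis plan, and their absence alone would be no finding. Here, though, the article itself fixes the populations, the withdrawal biopsy and the sizing, and these do not fit together.

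**Conclusion.** The concern holds in a conditional form. The article combines a one-dose ITT set, a biopsy at early withdrawal and a 12-month objective sized on about 300 women net of dropout, without fixing which denominator carries the primary part 2 result. For a given number of cases, admitting early negatives lowers the rate and its upper bound.

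The largest effect at the planned loss, with 2 cases, is a bound of 1.61% instead of 2.29%. That assumes all 117 leavers give an evaluable negative biopsy; realistic effects are smaller. Under a constant hazard with 10% to 30% stopping at a mean of 3 to 6 months, a true 1% would be estimated at 0.78% to 0.95%. The exposure times are assumptions. The planned per-protocol set does not settle the matter, because it can lose cases in women who withdraw.

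**What to change.** In Statistical analysis, define the primary part 2 incidence:

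- **Numerator:** women with hyperplasia or cancer found at any time on treatment.
- **Denominator:** women with an evaluable biopsy after the planned 12 months, within a stated window, plus any woman whose hyperplasia or cancer was found earlier.
- **Reported separately:** negative early-exit biopsies, with their exposure time.
- **Supporting:** the all-treated ITT rate and a woman-years rate.

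Keeping early cases while setting early negatives aside makes the denominator depend partly on outcome. That is a deliberately conservative choice for a safety endpoint and should be stated as such; other choices can be defended if fixed in advance. Part 2 is open-label, so the wording should be settled before the results are analysed.

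The cost is a change of analysis text, with no new data. The price is a smaller denominator and a somewhat less favourable upper bound.
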